## Methods

This study will be a randomized controlled trial, in accordance with the CONSORT statement for psychological interventions and the SPIRIT 2013 statement (47, 48). This study was funded by National Natural Science Foundation of China and Project of Humanities and Social Sciences, and registered in the clinicaltrial.gov (Clinical Trial No. NCT04965428, date assigned 23/07/2021). Ethics approval has been obtained from Ethics Committee of Shaanxi Provincial Cancer Hospital.

### Study design

The current study will compare Fear-focused Self-compassion Therapy with usual care in young women with breast cancer. A sample of 160 young female breast cancer patients with clinically significant FCR will be recruited from Shaanxi Provincial Cancer Hospital in Xi'an, China. After checking the eligibility of participants and completed the baseline measurement (T0), they will be randomized to either the Fear-focused Self-compassion Therapy or usual care control group. Four follow-up measurements will take place for both groups: immediately completing intervention (T1), after 3 months (T2), after 6 months (T3), and after 12 months (T4).

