**Methods:**

The Fear-focused Self-compassion Therapy consists of 8-week face to face group sessions. This study will be a randomized controlled trial with 160 Chinese young female breast cancer patients with severe FCR. Participants will be randomized to the therapy group or a usual care control group (1:1). Measurements will be completed at baseline, immediately completing intervention, 3, 6, and 12 months later. Primary outcomes are FCR severity, and secondary outcomes include symptoms of depression and anxiety, satisfaction with therapy, and cost-effectiveness of the therapy.

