### Aims of this study

In the current study, the Fear-focused Self-compassion Therapy, aiming to help Chinese young breast cancer patients to address FCR, has been developed. The primary aim of the current randomized controlled trial is to evaluate the effectiveness (i.e., both short-term and long-term effectiveness) and cost-effectiveness of Fear-focused Self-compassion Therapy in reducing severe FCR in young women with breast cancer, compared to usual care. Due to a lack of research comparing the cost-effectiveness between compassion-based therapy and usual care, it is hard to hypothesize which condition would be more cost-effective. This study expects that Fear-focused Self-compassion Therapy would be more cost-effective than usual care by reducing patients' FCR more effectively. Several specific hypotheses were outlined:

FCR severity would reduce to a larger extent in the Fear-focused Self-compassion Therapy condition (intervention group) compared to the treatment as usual condition (control group) from baseline and follow-up (3 months after treatment). The improvements in FCR can maintain at least 6 months after treatment.Symptoms of depression and anxiety would reduce to a larger extent in the Fear-focused Self-compassion Therapy condition compared to the treatment as usual condition from baseline and follow-up (3 months after treatment). These effects can maintain at least 6 months after treatment.Fear-focused Self-compassion Therapy would be cost-effective compared to treatment as usual.

The secondary aim of this study is to examine the underlying mechanisms of Fear-focused Self-compassion Therapy in reducing severe FCR. Specifically, the current research assumed that patients' improved dysfunctional cognitive evaluations and improved functioning of autonomic nervous system would play mediating roles between Fear-focused Self-compassion Therapy and improved FCR. Specific hypotheses are:

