### Intervention

The theoretical frame of the Fear-focused Self-compassion Therapy is based on the theories of FCR development as well as the theories of self-compassion related therapy such as compassion-focused therapy and mindful self-compassion therapy (31, 33, 38, 50, 51). The Fear-focused Self-compassion Therapy is an 8-week compassionate mind training intervention, and will be delivered as a group format. It is developed and tailored for Chinese young breast cancer patients by the authors including clinical psychologists, cancer nurses, and oncologists, adapted to be appropriate for Chinese young breast cancer patients and tailored to FCR. The therapy consists of eight group face-to-face sessions (60–90 min for each session) and will be delivered by three trained therapists for 8 weeks (sessions are weekly). The therapy will take place in Shaanxi Provincial Cancer Hospital, and each intervention group involves 10–15 patients. The content outline of intervention is shown in Table 1.

**Table 1 T1:** Content of fear-focused self-compassion therapy sessions.

**Session**	**Theme**	**Aims**	**Intervention content**
1.	The stability of attention	- Learn how to control the attention; - Recognize cancer-related thinking and worry; - Decrease over-identification.	- Introduce the plan, structure, confidentiality, and safety of intervention; - Introduce Fear-focused Self-compassion Therapy's theory; - Set the goals of intervention; - Introduce the attention; - Recall the experience of thinking in “automatic drive”; - Mindfulness meditation; - Discuss and set the aims, plans, and problems that may occur in home practice.
2.	Insight	- Observe your cancer-related thoughts and emotions; - Recognize your emotions and behaviors reacting to worry about cancer recurrence; - Experience the peace derived from the observation and non-involvement to the thoughts of cancer recurrence.	- Share your home practice and problems; - Deal with the problems left from last week; - Positive and negative thoughts, sensory training; - Stress response training; - Mind rest training; - Mindfulness meditation; - Image breath practice; - Discussion; - Renew the goals of home practice.

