8.	Be love and compassion with commitment	- Make a commitment to future life.	- Discuss the home practice; - Review the theory of self-compassion practice; - A summary of previous practice; - Set goals for home practice at the end of the intervention.

At the first session of the therapy, participants will obtain a pamphlet about the framework and goals of Fear-focused Self-compassion Therapy, as well as activities of each session. At the end of each session of the therapy, relevant home practice will be given to participants, and at the beginning of next session, these home practice will be reviewed to discuss participants' experience during home practice. When completing the therapy, participants will receive a handbook including the content of Fear-focused Self-compassion Therapy.

To make sure that all participants receive the same treatment, new participants should not be involved in the group if the intervention starts. Also, all participants are told that if they are absent for more than one session, they have to drop out this group and can choose other groups that has not started.

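### Follow-up visits in both arms are timed from completing the therapy, an event controls do not have and whose date in the therapy arm depends on group formation and attendance

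*Protocol article*

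**What the plan says.** **Schedule.** Under Study design, T0 is completed before randomisation. The follow-up visits are then fixed for both arms: "Four follow-up measurements will take place for both groups: immediately completing intervention (T1), after 3 months (T2), after 6 months (T3". The last visit, T4, comes at 12 months. The abstract uses the same anchor: "Measurements will be completed at baseline, immediately completing intervention, 3, 6, and 12 months later". Table 2, under Outcomes, labels T1 in the same way for everyone.

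**Origin of the later visits.** The sentence under Study design does not say what the months are counted from. Aims of this study does: the main hypothesis is worded "from baseline and follow-up (3 months after treatment") and continues "The improvements in FCR can maintain at least 6 months after treatment". Months therefore run from the end of treatment.

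**Controls.** Under Usual care, controls get no psychological intervention for fear of recurrence, so they have no end of treatment. No week, window or matching rule is given for their visits.

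**Therapy groups.** There are eight weekly sessions, and "each intervention group involves 10–15 patients". Groups are closed: "new participants should not be involved in the group if the intervention starts". The attendance rule reads: "if they are absent for more than one session, they have to drop out this group and can choose other groups that has not started".

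**Primary analysis.** Under Statistical analyses, FCRI severity is compared between arms at T1, T2, T3 and T4 in a linear mixed model adjusted for baseline score, sociodemographic and medical variables.

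**The concern.** A visit label gives a fair randomised comparison only if it means the same elapsed time in both arms and is set without regard to what happens after randomisation. Here the anchor is a post-randomisation event that exists in one arm only.

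Three things follow from the wording.

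- For controls, T1 to T4 have no defined date.
- For therapy patients, the date depends on how long a closed group takes to form and on whether the patient has to restart.
- A patient who leaves a group and does not restart never completes, so her T1 is undefined, as are the visits counted from it.

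The last two make the timing, and possibly the availability, of the primary outcome depend on attendance in one arm. If fear of recurrence changes over time for reasons unrelated to therapy, unequal elapsed time would enter the treatment contrast. Adjusting for the baseline score does not remove this, because that adjustment addresses differences in starting level and not in time elapsed.

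**Working it through.** The article states no figure for visit timing, so there is none to reproduce. Its one computed figure, the sample size, does reproduce: a two-sample t-test with d = 0.49, two-sided alpha 0.05 and power 0.80 needs 66.35, so 67 per arm and 134 in total. This point does not affect it.

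**Inputs from the article:** 8 weekly sessions; closed groups of 10–15; 80 patients per arm, hence 80/15 = 5.3 to 80/10 = 8, or about 6 to 8 therapy groups; T0 before randomisation; a second absence means leaving, with the option of a group not yet started.

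**1. Delay from restarting.** Count weeks from the start of the first group, with session s in week s. Without a switch, T1 falls at week 8. Suppose the second absence is at session s (s = 2 to 8). Any group still open to her has not started, so she faces eight further sessions. If it starts the very next week, its last session is in week s + 8, and the delay is (s + 8) − 8 = s weeks.

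| Second absence at session | Earliest T1 (week) | Delay (weeks) |
|---|---|---|
| 2 | 10 | 2 |
| 3 | 11 | 3 |
| 4 | 12 | 4 |
| 5 | 13 | 5 |
| 6 | 14 | 6 |
| 7 | 15 | 7 |
| 8 | 16 | 8 |

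T2, T3 and T4 are counted from T1 and move by the same amount. These are minimum delays, because any wait for the next group adds to them.

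**2. How many could trigger the rule.** The article gives no absence rate. Assume independent absences with probability p per session. Then P(at least 2 of 8) = 1 − (1 − p)^8 − 8p(1 − p)^7.

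- p = 5%: 5.7%, or about 5 of 80
- p = 10%: 18.7%, or about 15 of 80
- p = 15%: 34.3%, or about 27 of 80

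These are patients who would have to leave a group. How many would restart is unknown.

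**3. Waiting for a group to fill.** Accrual is not given either. If patients are randomised one at a time at r therapy-arm patients per week, the first in a group of g waits (g − 1)/r weeks, and the average wait is half that.

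| Assumed r per week | First patient's wait, g = 10 to 15 (weeks) | Average wait (weeks) |
|---|---|---|
| 1 | 9 to 14 | 4.5 to 7 |
| 2 | 4.5 to 7 | 2.25 to 3.5 |
| 4 | 2.25 to 3.5 | 1.1 to 1.75 |

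**4. Time from T0 to T1.** With no wait and no switch, it is about 8 weeks in the therapy arm. With a 7-week wait (r = 2, g = 15) and a second absence at session 8, it is at least 7 + 16 = 23 weeks. For controls it cannot be worked out, because their T1 has no date.

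**The case against.** The strongest reply is that the article describes one schedule for all participants, and that the natural reading is that controls are measured in step with a concurrent therapy group. How control visits are dated is a detail that a full protocol could well contain, and a journal article condenses. Randomisation might also be done in batches just before a group starts, which would remove most of the wait. The article does not say.

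Much of this stands, and it rules out three stronger readings.

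- *That the arms are in fact compared at different times.* The text leaves this possible but does not state it. The wait for a group is likewise inferred from closed groups of 10–15.
- *That a bias of known size follows.* A reader might assume a decline of 0.05 SD per month over a wait of 1 to 3 months and arrive at 0.05 to 0.15 SD, which is 10–30% of the planned 0.49. The article supports neither input. The figure also requires controls to be measured with no matching delay, which is the open question. Regression to the mean from selecting on a severity score of 13 or more does not supply a monthly slope: it appears largely at the next measurement, in both arms.
- *That women who leave a group are not assessed.* The article does not say so. It says only when T1 happens, in terms that do not fit them.

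The reply does not remove the core. The article does not merely omit an anchor for controls. It states one for both arms that cannot apply to them, and its own restart rule moves that anchor in the therapy arm according to attendance.

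**Conclusion.** The point holds as a defect in how the visit schedule is fixed. Completion of therapy is the stated origin of T1 to T4 in both arms, yet it does not exist for controls and varies with group formation and attendance in the therapy arm. Read literally, the restart rule delays T1 to T4 by 2 to 8 weeks or more for those who use it, and leaves those who do not restart without a T1. Because the primary comparison is by visit label, time since baseline may differ between arms and depend on attendance.

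The 2 to 8 weeks assume that T1 is re-dated for patients who restart, as the wording implies, and that a new group starts at once. The absence and accrual figures are illustrations under stated assumptions. The direction and size of any bias cannot be computed from the article, and no sample-size figure changes.

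**What to change.** Set T1 to T4 in both arms from one anchor that does not depend on attendance. One workable choice is the start date of the therapy group to which a patient is first assigned, with each control tied to the dates of a concurrent group. T1 is then at the end of week 8, and T2, T3 and T4 are 3, 6 and 12 months after that, each with a visit window.

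State that every randomised participant is assessed on those dates whether or not she attended, left or moved group, and that she is analysed in her randomised arm. Taking T0 and randomising shortly before a group starts would also shorten the wait. That is optional, and it would be more than a wording change because it alters the allocation procedure and must work with the stratification.

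The cost is modest. Control visits have to be coordinated with group dates, and some patients who move group will be assessed before they finish therapy. For them the hypotheses worded as months after treatment should be restated as months after the scheduled end of treatment. The attendance rule itself need not change.

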### Participant eligibility

Women are eligible to participate if they: (1) are diagnosed with breast cancer (including various cancer stages and subtypes); (2) are aged 18–45 years; (3) can sign written informed consent; (4) can read and write Chinese; and (5) have clinically significant FCR, with scores ≥13 on the FCRI severity subscale (49).

If participants have a cancer recurrence during the study, they would remain in the therapy group, but their data would not be included in the final data analysis. Women are ineligible to participate if they: (1) currently have psychiatric and psychological illness; (2) have other types of tumor; (3) had a previous cancer recurrence; and (4) are participating another psychological intervention at the start of the study or during their 8-week therapy.

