## Introduction

Globally, breast cancer has become one of the highly prevalent cancers in women (1). Similarly in China, the number of women being diagnosed with breast cancer is increasing, partly because of early screening and improved medical treatments (2). It is estimated that 0.37 million Chinese women are living with and beyond breast cancer in 2018 (2). About 20% of Chinese women with breast cancer are young people aged from 18 to 40 (3). Compared with older cancer patients, younger patients concern more about cancer recurrence or cancer progress (4–6). Especially for young breast cancer patients, they are more likely to have lymph node metastasis, an advanced cancer stage, a high histological grade, and a larger mass (7). Moreover, young breast cancer patients tend to choose breast conserving therapy for the consideration of future life (8). These can increase the risks of cancer recurrence and transference, which may cause clinically significant Fear of Cancer Recurrence (FCR). FCR has been found as one of the major psychological problems in young breast cancer patients (6, 9, 10). Up to 70% of young breast cancer patients suffer from clinically significant FCR (11). Therefore, it is of great clinical relevance to offer young breast cancer patients effective psychological interventions to address FCR.

FCR is defined as the fear and worry about cancer returning or cancer progress (12). FCR can be considered as a concern that may range on a continuum from mild and short-term normal fear to severe and long-term pathological fear (5). Mild FCR is adaptive, as it can prompt patients to be alert to their body symptoms (13), and increase patients' awareness of self-protection and adherence to treatment (14). Yet, severe pathological FCR may not only cause patients' overuse of primary care that increases unnecessary healthcare cost (15), but also lead to patients' intrusive thoughts, re-experienced trauma, hypervigilance, avoidance of cancer related memory, and difficulties in future planning (16, 17). This may negatively influence patients' quality of life, prognosis, and even survival (18).

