### Statistical analyses

The aim of the primary analysis is comparing the Fear-focused Self-compassion Therapy group with usual care control group on the score of FCRI severity subscale. In the primary analysis, post-treatment scores will be compared between two groups at four measurement time points (T1, T2, T3, and T4). Analysis will be performed by using linear mixed models, including baseline scores, sociodemographic and medical variables as covariates.

The aim of secondary analysis is to test the mediating role of improved dysfunctional cognitive evaluation and improved functioning of autonomic nervous system between Fear-focused Self-compassion Therapy and improved FCR. Analysis will be performed by using multilevel structural equation model, including baseline scores, sociodemographic and medical variables as potential covariates.

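### Participants whose cancer recurs after randomisation are left out of the final analysis, and it is unclear whether this applies in both arms

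*Protocol article*

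**What the plan says.** Under Participant eligibility, the rule opens with "If participants have a cancer recurrence during the study" and continues that "they would remain in the therapy group, but their data would not be included in the final data analysis". A recurrence before entry is dealt with separately, as a screening exclusion for women who "had a previous cancer recurrence".

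Study design fixes the order of events: "After checking the eligibility of participants and completed the baseline measurement (T0), they will be randomized". Four follow-up measurements come after that, the last at 12 months.

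Under Statistical analyses, the primary comparison is on the FCRI severity subscale by linear mixed models at T1 to T4. That section names no analysis set, and nothing elsewhere in the article keeps participants with a recurrence in any analysis. The sample size section allows for dropout and does not mention these exclusions.

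**The concern.** Recurrence before entry is already screened out, so the rule acts on events during follow-up, after allocation. Three things follow.

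- **The comparison is no longer between the groups as randomised.** The event that triggers removal is the very thing the primary outcome measures fear of. The women removed are unlikely to be a random subset.
- **Valid data are lost.** A woman whose cancer recurs at month 11 loses her T1, T2 and T3 scores, all measured before the event. A linear mixed model can use incomplete series, so the planned analysis does not need this.
- **The scope is unclear.** The sentence speaks of staying in the therapy group and does not mention controls. If only therapy-arm patients were removed, and recurrent patients have higher fear scores, the therapy would look better than it is.

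This is a stated rule, not a detail left to an analysis plan. A plan written to follow the protocol would carry it forward.

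**Working it through.** **Inputs from the article.** Sample size calculation: d = 0.49, two-sided alpha 0.05, power 0.80, 134 evaluable (67 per group), 160 randomised (80 per group), 20% added for dropout.

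**Inputs assumed.** The article gives no recurrence rate and no score difference for recurrent patients. A recurrence rate of 3-8% over the study is assumed, and a score 0.5 to 1.0 SD higher in patients with a recurrence.

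**1. The plan's own figure.** By the two-sample t test (noncentral t), 67 per group gives power 0.804 and 66 gives 0.798, so 134 is reproduced. Adding 20% gives 134 × 1.20 = 160.8, in line with the stated 160.

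**2. Loss of power.** After 20% dropout, 160 × 0.80 = 128 remain, with power 0.785. Recurrence exclusions are applied to those 128:

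| Assumed recurrence | Remaining | Power at d = 0.49 |
|---|---|---|
| 0% | 128 | 0.785 |
| 3% | 128 × 0.97 ≈ 124 | about 0.77 |
| 8% | 128 × 0.92 ≈ 118 | about 0.75 |

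The loss is at most about 3.5 percentage points. That the starting value is already below 0.80 comes from how the dropout allowance was added and is a separate matter.

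**3. Bias if both arms are deleted.** Let p be the recurrence proportion in an arm and k the amount, in SD, by which recurrent patients score higher, taken as equal in both arms. The deleted result differs from the all-randomised result by (p in control − p in therapy) × k. With equal proportions this is 0.

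Illustrative unequal case: 20% of each arm is high-risk and scores 1 SD higher; recurrence occurs only among them, and is detected in 20% of them in one arm and 40% in the other.
- High-risk share retained, first arm: 0.20 × 0.80 / (1 − 0.04) = 0.16 / 0.96 = 0.167.
- High-risk share retained, second arm: 0.20 × 0.60 / (1 − 0.08) = 0.12 / 0.92 = 0.130.
- Shift: 0.167 − 0.130 = 0.036 SD before rounding, and 0.036 / 0.49 = 7%.

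The direction depends on which arm has more detected recurrences.

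**4. Bias if only the therapy arm is deleted.** With no true effect and the same recurrence proportion r in both arms, the control mean carries r × k and the therapy mean does not. The spurious benefit is r × k. The type I error below uses a normal approximation with 80 controls and 80 × (1 − r) therapy patients, ignoring dropout.

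| r | r × k for k = 0.5 to 1.0 | Share of 0.49 | Two-sided type I error |
|---|---|---|---|
| 5% | 0.025-0.05 SD | 5-10% | 0.053-0.061 |
| 10% | 0.05-0.10 SD | 10-20% | 0.061-0.094 |

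At equal rates, then, two-sided deletion gives no bias and one-sided deletion gives a bias that favours the therapy. The 10% row lies above the 3-8% range and shows how the bias grows.

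**The case against.** The strongest defence is that the effect is probably small and that recurrence changes what a fear-of-recurrence scale measures. Women with a previous recurrence are barred at entry, so the target population is recurrence-free, and scores after a recurrence could reasonably be treated differently. That stands as far as it goes: including post-recurrence scores in the primary analysis is one defensible choice of estimand, not the only one. It does not justify deleting the scores taken before the event.

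Four stronger readings are tempting, and the article does not support them.

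- **That the therapy will change who is found to have a recurrence.** The Introduction says "Mild FCR is adaptive, as it can prompt patients to be alert to their body symptoms", but it describes severe fear separately, as leading to overuse of care and to avoidance. The trial enrols women with clinically significant fear. Nowhere does the article say that lowering severe fear alters detection, or in which direction. This is a hypothesis only.
- **That exclusion (4) has the same defect.** It covers women who "are participating another psychological intervention at the start of the study or during their 8-week therapy". The wording does reach past randomisation, but it is listed as an eligibility criterion and says nothing about removing data. Other psychological therapy is already recorded in the resource use diary.
- **That only therapy-arm patients are deleted.** The opening of the sentence refers to participants in general, and staying in the therapy group may simply mean continuing with the sessions. The text is ambiguous; one-sided deletion is a possibility, not an established plan.
- **That the bias is large.** Every bias figure above rests on assumed inputs, and with both arms treated alike it may be close to zero.

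**Conclusion.** The point holds. The article states an exclusion based on an event after randomisation, tied to the primary outcome, with no analysis that retains the patients concerned. It discards valid pre-recurrence scores and leaves it unclear whether both arms are treated alike.

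The likely size is modest. Power falls by one to three and a half percentage points if 3-8% recur. The effect estimate is barely affected if deletion, recurrence rates and recurrent patients' scores are alike in the two arms. One-sided deletion is the more serious case, since it favours the therapy even with equal recurrence rates. The balance between arms cannot be known in advance.

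The rule should be changed before analysis because it compromises the primary randomised comparison and is easily corrected, not because a large bias has been shown.

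**What to change.** Replace the data-exclusion part of the recurrence sentence with wording such as: all randomised participants are analysed in their assigned arm; all FCRI scores before a recurrence are used in the mixed model; scores after a recurrence are handled by one prespecified rule applied identically in both arms; recurrences are reported by arm. One suitable rule is to include later scores in the primary analysis and set them to missing in a sensitivity analysis. Nothing here bears on whether a participant continues in the therapy sessions.

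The cost is a sentence or two in the protocol and the analysis plan. No new data, visits or participants are needed. If post-recurrence scores are included, late scores will be slightly more variable.
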